### 3. RATIONALE / BACKGROUND

Type 1 diabetes (T1D) is an autoimmune condition characterised by pancreatic beta cell destruction and absolute insulin deficiency. Individuals living with T1D must inject insulin multiple times a day to survive and can experience serious daily challenges associated with manual regulation of blood glucose levels. Modern T1D management is primarily focused on reducing risk and burden of chronic disease, including cardiovascular diseases, since the discovery of insulin in 1921 has extended the lives of individuals affected [1]. Achieving a haemoglobin A1c (HbA1c) of  $\leq 7.0\%$  is therefore the primary management target in diabetes [1] as it is associated with reduced risk of developing chronic complications related to hyperglycaemia [2]. However, the high amounts of exogenous insulin commonly being used to achieve glycaemic control targets in people with T1D also has long-term health consequences, including hyperinsulinemia, which is associated with obesity, the metabolic syndrome and atherosclerosis [3, 4]. Ultimately, adjunctive therapies that achieve glycaemic control *and* minimise reliance on excessive insulin are needed to improve the health and wellbeing of individuals living with T1D.

The varying impact of dietary factors on blood glucose levels is well-known, yet there remains a lack of consensus surrounding the optimal dietary approaches to achieve glycaemic control in T1D. Standard treatment involves multiple daily injections of insulin, wherein the dose of meal-time insulin is calculated based on the estimated grams or portions of carbohydrate consumed. Leading health authorities, including the National Health & Medical Research Centre (NHMRC), have traditionally recommended a high-carbohydrate (HC) diet, contributing 45-65% total energy intake (TEI), although this recommendation has been inferred from National Dietary Guidelines for the general population who are free from diabetes [1]. Data from T1D registries across 19 countries in Australasia, Europe and North America (n = 324,501) reported that 84% of patients exhibited HbA1c above the desirable target range (>7.0%) [5] suggesting that the current dietary advice for T1D is achieving limited impact and alternative dietary approaches should be considered.

A separate body of evidence conducted in type 2 diabetes (T2D) shows that diets containing less than 45% TEI from carbohydrates are effective for improving glycaemic control and CVD risk. Multiple systematic reviews have demonstrated that, when compared to usual care HC diets, diets <45% TEI from carbohydrates achieve greater reductions in HbA1c and use of diabetes medications [6-8] in addition to more favourable changes in blood lipid profile, including greater increases in HDL-cholesterol and decreases in triglycerides [8]. Moreover, there is a reported dose-response effect such that HbA1c is lower with greater carbohydrate restriction [6, 7]. Low-carbohydrate (LC) diets are not clearly defined in the scientific literature but in a recent systematic review (conducted by members of this team), which is the largest systematic review of all LC diets for T2D management available to-date (n=41; including all interventional study designs), LC diet interventions were defined as diets containing ≤130 g/day or 26% TEI from carbohydrate [9]. One 2-year trial (conducted by members of this team) compared a LC diet (14% TEI as carbohydrate) with a traditional HC diet (53% TEI as carbohydrate) in individuals with T2D and achieved greater reductions in diurnal glycaemic variability and diabetes medications alongside improvements in multiple CVD risk markers [10]. This cumulative evidence has led to recent updates to clinical practice guidelines globally, with acceptance of LC diets as an effective therapeutic option for T2D management by national organisations, including Diabetes Australia, Diabetes UK and the American Diabetes Association [11-13].

In response to this, the interest in LC diets for T1D management has increased. Qualitative evidence has found that many patients with T1D self-restrict carbohydrates, reporting that large amounts of carbohydrates coupled with large doses of required insulin lead to

unpredictable blood glucose levels [14]. Another study reported that a lower intake of dietary carbohydrates was associated with lower HbA1c levels in outpatients with T1D [15]. Members of this research team recently published the first systematic review of diets <45% TEI from carbohydrates for T1D management and nine studies were included (RCTs=2; pre-post interventions=4; retrospective case-series analyses=2; case-report=1) [16]. Six studies reported a mean reduction in HbA1c with diets <45% TEI from carbohydrates, with three statistically significant reductions ( $P<0.05$ ) [16]. The LC diet arms ( $\leq 26\%$  TEI from carbohydrates) also resulted in a reduced need for exogenous insulin while maintaining (or improving) glycaemic control [16]. One small RCT of 10 adults reported a 33% reduction in the mean total daily insulin use (TDI) with a LC diet (50-75 g/day) compared to no change with a diet higher in carbohydrates (~204 g/day) [17]. Another small RCT of 14 adults with T1D showed similar results [18]. No study in our review reported any statistically significant change in the negative direction for any T1D management outcome with a LC diet [16]. However, due to the significant heterogeneity, small sample sizes and quality of included studies, an overall effect of diets LC diets on T1D management could not be determined and additional research is needed.

Preliminary evidence suggests that LC diets appear safe for use in T1D and may be effective for certain subgroups of this clinical population. However, the available body of research is limited and there is still a lack of consensus regarding the efficacy of LC diets for improving T1D management. Since there are a multiplicity of lifestyle factors impacting T1D management [19], and with consideration that all individuals have their own personal needs and preferences, an interventional study that uses participants as their own controls and investigates a patient-led dietary approach will be of important clinical relevance. Therefore, a within-patient interventional study investigating a LC diet with an adaptive carbohydrate prescription (25-75 g/day) will be undertaken in adults with T1D in an outpatient setting.

#### **4. AIMS / OBJECTIVES / HYPOTHESES**

The aim of this research is to assess the efficacy of a LC diet in adults with T1D. Our primary objective is to determine the effects of a LC diet (25-75 g/day) on clinical markers of T1D management including HbA1c, glycaemic variability, frequency of hypoglycaemia, TDI, and quality of life.

In adults with T1D, compared to a habitual diet that is higher in carbohydrates, a LC diet will result in:

- improved glycaemic control (lower HbA1c, reduced glycaemic variability, reduced frequency of hypoglycaemia)
- reduced TDI requirements (wherein the reduction is expected to come primarily from meal-time insulin doses)
- improved quality of life and satisfaction with diabetes management

## 5. PARTICIPATING SITES

This project will include both online (Telehealth) and in-person contact. Online visits will be conducted via Telehealth using Zoom video conferencing (<https://zoom.us>). Clinic visits will be conducted from a private clinic room at the Susan Wakil Health Building (The University of Sydney, [name]). There is opportunity for fully remote participation in this study, if required or preferred. In addition, this study provides opportunity for a member of participants' usual diabetes care team to be involved. Before entry into the study, participants will be required to nominate one member of their usual diabetes care team who is proficient in insulin management (i.e., an endocrinologist, a general practitioner or a diabetes educator). The nominated healthcare practitioner (HCP) will be made fully aware in writing of their patient's intention to participate in the study and details of the intervention. The HCP will be asked to confirm their ability and willingness to provide ongoing support (usual care) and medical oversight (specifically, management of insulin therapy) to their patient(s) throughout the duration of the intervention from their usual practice location or via Telehealth on an as-needed basis.

## 6. RESEARCH PLAN / STUDY DESIGN

### 6.1 Type of study

A 28-week single arm, within-participant controlled intervention study.

### 6.2 Population / sample size

The primary outcome is HbA1c. Based on a clinically relevant difference in HbA1c of 0.7% (absolute) with a standard deviation of 1.0 [17], to achieve 80% power with  $\alpha < 0.05$ , we require a sample size of  $n=16$ . Anticipating a 20% dropout rate, we plan to recruit 20 participants into the study.

However, as this study is part of a PhD project, we've only got time and resourcing to have a recruitment period of 5 months. The recruitment period will end at 5 months and the study will continue, irrespective of the number of participants recruited up until that point (Table 2).

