### **6.3 Statistical analyses**

Data will be analysed using the most up-to-date version of SPSS. Outcome results will be presented as means and standard deviations. One-Way Analysis of Variance (ANOVA) will be used to assess the within group differences across time for each outcome.

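### Section 6.2 states 80% power with 16 completers, but that n is a large-sample figure: if 1.0 is the SD of within-person change, a two-sided paired t-test has about 74%

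*Protocol*

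**What the plan says.** HbA1c is the only primary outcome (Protocol 9.1). Section 6.2 bases the sample size on it: "Based on a clinically relevant difference in HbA1c of 0.7% (absolute) with a standard deviation of 1.0 [17], to achieve 80% power" at an alpha below 0.05, which leads to n=16. A 20% dropout allowance raises this to 20 recruits. The section does not name the test, say whether it is one- or two-sided, or say whether 1.0 is the SD of the change within a person or the SD of HbA1c values between people.

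The same section ends recruitment at five months "irrespective of the number of participants recruited up until that point".

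Section 6.3 says "One-Way Analysis of Variance (ANOVA) will be used" for differences over time inside the group. Section 6.1 describes one arm with each participant as their own control. Section 9 sets three main measurement points (before control, before intervention, after intervention), with HbA1c taken again at the 12-week follow-up.

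**The concern.** The stated n matches a formula that treats the SD as known. With 16 people the SD has to be estimated from the data, and the allowance for that is no longer negligible. If the 80% is too high, a non-significant HbA1c result would be read as stronger evidence against a 0.7% effect than the trial can supply.

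Two gaps make the figure harder to interpret. Power depends strongly on which SD the 1.0 is. And the test named in 6.3, as worded, is not clearly the test that was sized in 6.2.

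**Working it through.** **Inputs.** Difference 0.7, SD 1.0, power 80%, alpha 0.05, n=16, dropout 20% (all section 6.2). Single arm, within participant (6.1). Three main time points (section 9). Two-sided testing is my assumption, because 6.2 does not state sidedness.

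**1. The plan's own figure.** Normal formula for one mean change:

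n = ((z₀.₉₇₅ + z₀.₈₀) × SD / difference)² = (1.960 + 0.842)² / 0.7² = 7.849 / 0.49 = 16.02.

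Rounded down, this is 16. The same approximation puts power at n=16 at Φ(0.7 × √16 − 1.960) = Φ(0.840) = 79.96%. The dropout step is right: 16 / 0.8 = 20. So the plan's figures follow from this formula, taking 1.0 as the SD of change.

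**2. The same comparison as a paired t-test.** With n=16 there are 15 degrees of freedom, so the critical value is 2.131 instead of 1.960. The noncentrality is 0.7 × √16 / 1.0 = 2.8. The noncentral t-distribution gives:

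| Completers | Power at 0.7% | Difference detectable with 80% power |
|---|---|---|
| 10 | 51% | 1.00% |
| 12 | 60% | 0.89% |
| 16 | 74.5% | 0.75% |
| 18 | 79.9% | 0.70% |
| 19 | 82.3% | 0.68% |
| 20 | 84.4% | 0.66% |

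The shortfall at 16 is about 5.5 percentage points. At least 80% takes 19 completers, and at the plan's dropout rate 19 / 0.8 = 23.75, or 24 recruits.

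**3. If 1.0 is the SD of HbA1c levels.** The SD of change is then 1.0 × √(2(1 − ρ)), where ρ is the correlation between the two measurements. The protocol gives no ρ, so I show a range (n=16, two-sided paired t):

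| ρ | SD of change | Power |
|---|---|---|
| 0.3 | 1.18 | 60% |
| 0.5 | 1.00 | 74.5% |
| 0.6 | 0.89 | 83% |
| 0.7 | 0.77 | 92% |

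**4. The ANOVA in 6.3.** Take three time points with mean changes 0, 0 and −0.7. The squared deviations from their mean sum to 0.327.

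- *Repeated-measures reading.* With an SD of change of 1.0, the within-person error variance is 1.0² / 2 = 0.5. The noncentrality is 16 × 0.327 / 0.5 = 10.45 on 2 and 30 degrees of freedom. Power of the overall test is 79.2% under sphericity, 69.8% at epsilon 0.75 and 57.1% at epsilon 0.5, the lower bound for three time points. If the means instead fall evenly (0, −0.35, −0.7), it is 66.1% under sphericity.
- *Independent-groups reading.* With an SD of 1.0 at each visit, the noncentrality is 16 × 0.327 / 1.0 = 5.23 on 2 and 45 degrees of freedom. Power is 49.4% if the data really were independent, and about 44% by simulation when measurements on the same person correlate at 0.5.

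The 79.2% belongs to the overall three-point test. The post-intervention minus pre-intervention difference, tested alone as a paired comparison, has the 74.5% of step 2.

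**The case against.** The best defence is that n=16 is not a slip. It follows from the stated inputs by a standard formula, and the gap is two to three completers: 18 give 79.9%, and if all 20 recruits finish, power is 84.4%. That accounts for the number, but 16 completers still do not give 80% on a two-sided paired t-test. A one-sided test at 5% would give 84.7%, but none is stated.

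The defence also notes that 74% rests on reading 1.0 as the SD of change, and that on the other reading 80% could be too low as easily as too high. That stands. The 74% must be quoted with its assumption, and the SD type has to be named.

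Three stronger readings are tempting, and the documents do not support them:

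- **Power is really 44–49% because 6.3 names One-Way ANOVA.** That requires treating repeated measurements on the same people as separate groups. Section 6.3 speaks of change over time inside the group and 6.1 of a within-participant design, so repeated measures is the natural reading, with about 79% under sphericity.
- **The SD is so uncertain that power may be 30%.** Section 3 describes the cited source thus: "One small RCT of 10 adults reported a 33% reduction in the mean total daily insulin use". If all 10 people informed the SD, its 95% interval would be 0.69 to 1.83. The protocol does not say how many did, and the other end of that interval gives about 97%.
- **The five-month recruitment stop is an error.** It is disclosed with its reason and repeated in section 11. It is a declared feasibility limit, although its effect on power is not stated.

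**Conclusion.** The point holds in a limited form. The 80% in 6.2 is a large-sample approximation. For a two-sided 5% paired t-test with an SD of change of 1.0, 16 completers give about 74%. Put another way, the difference detectable with 80% power is 0.75% and not 0.70%. The shortfall is modest, and it depends on two things the protocol leaves open: sidedness and the type of SD. The SD type matters more, since power at 16 ranges from 60% to 92% if 1.0 describes HbA1c levels and the correlation lies between 0.3 and 0.7.

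Section 6.3 has a wording gap, not a demonstrated loss of power. Read as repeated measures, the overall test comes close to the stated 80% if sphericity holds, and falls short if it does not. Run literally as an independent-groups One-Way ANOVA, it would ignore the pairing and have about 44–49%. The wording should rule that out.

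**What to change.** Keep 20 recruits and restate section 6.2 along these lines:

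> Assuming an SD of within-person change of 1.0, 16 completers give about 74% power (paired t-test, two-sided 5%) to detect 0.7%, or 80% power to detect 0.75%. If recruitment closes early, 12 completers give 60% and 10 give 51%.

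Confirm from the cited source that 1.0 is the SD of change. If it is the SD of levels, say so, state the assumed correlation and recompute.

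In section 6.3, name the ANOVA as repeated-measures (within-participant), and name the post-intervention minus pre-intervention difference in HbA1c as the comparison the sample size refers to. If the overall test is also quoted, give its roughly 79% at n=16 as conditional on sphericity and three time points.

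The cost is a slightly less favourable stated figure. No extra participants, visits or measurements are needed.

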### **6.3 Statistical analyses**

Data will be analysed using the most up-to-date version of SPSS. Outcome results will be presented as means and standard deviations. One-Way Analysis of Variance (ANOVA) will be used to assess the within group differences across time for each outcome.

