### 7.3.2 Hypoglycaemia

Hypoglycaemia is a common acute complication of T1D which generally results from the difficulties in predicting expected rises in blood glucoses levels and accurately calculating insulin requirements. Due to the expected change(s) in insulin requirements as a result of the diet intervention, there is a risk of participants miscalculating their insulin requirements in the early stage of the intervention which could lead to increased frequency and/or severity of hypoglycemia. This will be mitigated by close monitoring of blood glucose levels, regular contact with the study dietitian, ongoing support from a nominated HCP, and oversight/supervision by the study physician, study diabetes educator and study endocrinologist.

Hypoglycaemia is defined by Diabetes Australia as a blood glucose level below 4 mmol/L [27]. The resources developed by the study dietitian and diabetes educator titled 'Managing hypoglycaemia' (Attachments 42 and 48) provide participants with information and guidelines on preventing and/or managing hypoglycaemia during the study. Participants will be required to test their blood glucose levels at least six times every day (i.e., before and 2 hours after each meal) using their own glucose monitoring

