## 9. OUTCOMES

All primary, secondary and additional outcomes will be measured at three time-points: (1) pre-control period, (2) post-control period / pre-intervention period, and (3) post-intervention period. The only data being collected at follow up (12 weeks post-intervention) is HbA1c, total daily insulin (previous 24 hours), dietary intake (previous 24 hours), diabetes-related quality of life and diet satisfaction. Refer to Table 1 for a clear description of what outcomes are being measured at what time-points throughout the duration of the study for each participant. Refer to Figure 1 for an overview of this information.

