### 9.2 Secondary outcomes

- Glycaemic variability (GV) markers (including Standard Deviation (SD) intraday and mean amplitude of glycaemic excursions (MAGE) [derived from 7-day CGM/FGM data]
- Frequency of hypoglycaemia (<3.5 mmol/L with or without symptoms) [derived from 7-day CGM/FGM data]
- Total daily insulin (TDI) [the sum of all long-acting and rapid-acting insulin given over a 24-hour period derived from a 3-day self-report insulin log]
- Quality of life [measured using the 15-item DQOL Brief Clinical Inventory [25]]

GV markers have been identified as independent risk factors for diabetes complications including CVD, underscoring the importance of this assessment to more rigorously evaluate the effect(s) of the diet intervention on diabetes management.

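### Section 6.3 fixes means, SDs and a one-way ANOVA for 7-day hypoglycaemia frequency; run literally this ignores pairing and may have very low power, and under any reading mean and SD suit a skewed count poorly

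*Protocol*

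**What the plan says.** Section 6.3 sets one presentation, "Outcome results will be presented as means and standard deviations", and one test: "One-Way Analysis of Variance (ANOVA) will be used to assess the within group differences across time for each outcome". Neither sentence makes an exception for counts or skewed data.

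Section 9.2 lists among the secondary outcomes "Frequency of hypoglycaemia (<3.5 mmol/L with or without symptoms) [derived from 7-day CGM/FGM data". Section 9 adds that "All primary, secondary and additional outcomes will be measured at three time-points": before the control period, after it, and after the intervention. Hypoglycaemia is not collected at follow-up.

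Section 6.1 describes the design as "A 28-week single arm, within-participant controlled intervention study", so the three counts come from the same people.

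The outcome matters in both directions. Section 4 expects "improved glycaemic control (lower HbA1c, reduced glycaemic variability, reduced frequency of hypoglycaemia". Section 7.3.2 warns of insulin miscalculation early in the intervention, "which could lead to increased frequency and/or severity of hypoglycemia", and section 8.1 lists more frequent hypoglycaemia among the adverse events.

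**The concern.** A weekly episode count in about 16 people is likely to be low, bounded at zero and right-skewed, with a few participants contributing many episodes. Two features of section 6.3 fit it badly.

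- **The test.** A one-way ANOVA run as named treats the three occasions as separate groups. Stable differences between people then sit in the error term and can bury the within-person change that the design exists to measure.
- **The summary.** Mean and SD describe a skewed count poorly. A raw-count ANOVA also yields no direct estimate of the change with an interval.

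At stake is a non-significant result being read as no change in hypoglycaemia, when the test could have missed a material fall or rise.

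**Working it through.** **The plan's only power figure.** Section 6.2 covers HbA1c alone: difference 0.7, SD 1.0, 80% power, alpha 0.05. The paired normal approximation gives (1.0 × (1.960 + 0.842) / 0.7)² = 16.02, which matches the stated 16; 16 / 0.80 = 20 recruited. No such figure is given for hypoglycaemia.

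**Inputs for hypoglycaemia.** From the protocol: 16 completers, three time points. Assumed, because the protocol is silent: person rates follow a gamma distribution with mean μ = 3 or 5 per week and shape k = 1 or 0.7 (CV = 1/√k = 1.0 or 1.2). There is a week-to-week gamma multiplier of shape 8 and the counts are Poisson. The diet multiplies the week 16 rate by 0.5, 1 or 1.8.

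**What these inputs imply.** The variance of one count is μ + μ²[(1 + 1/k)(1 + 1/8) − 1].
- k = 1, μ = 5: 5 + 25 × 1.25 = 36.25, so SD 6.02 and SD/mean 1.20.
- k = 0.7, μ = 3: 3 + 9 × 1.732 = 18.59, so SD 4.31 and SD/mean 1.44.

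SD/mean averages somewhat lower in samples of 16, at 1.1-1.3. It still exceeds 1, so mean minus one SD falls below zero for a count that cannot be negative.

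The correlation between two weeks in the same person is (μ²/k) / variance.
- k = 1, μ = 3: 9 / 14.25 = 0.63.
- k = 0.7, μ = 5: 35.7 / 48.3 = 0.74.

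With no true change, the time mean square in an independent-groups ANOVA has expectation σ²(1 − ρ), while the error mean square has expectation σ². Their ratio is therefore about 0.26-0.37 instead of 1, against a 5% critical value of about 3.2 on 2 and 45 degrees of freedom. That is why the literal test almost never rejects.

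**Simulated rejection rates** (2,000-4,000 trials per setting, nominal 5%):

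| Analysis | Rate halved | Rate × 1.8 | No change |
|---|---|---|---|
| One-way ANOVA, independent groups | 4-9% | 6-15% | 0-0.2% |
| Repeated-measures ANOVA, raw counts | 42-63% | 50-69% | about 4-5% |
| Same, Greenhouse-Geisser corrected | 35-55% | 45-62% | – |
| Signed-rank, week 16 minus week 4 | 49-67% | 51-69% | about 5% |
| Unpaired rank tests | 5-18% | 2-12% | – |

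Unpaired rank tests do little better than the literal ANOVA, while a paired normal-theory ANOVA comes close to the signed-rank test. Pairing, not normality, explains nearly all of the gap.

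**Sensitivity to the assumptions.** Lowering the between-person CV to about 0.7 in the same model lifts the literal test to 25-39%. A wider grid used means of 2, 5 or 10 per week, CV 0.7 or 1.0, and either pure Poisson counts or extra weekly variation of gamma shape 3:

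| Change | Literal one-way | Repeated measures (uncorrected) |
|---|---|---|
| Halved | 6-52% | 25-100% |
| 30% fall | 0-5% | 10-76% |
| 50% rise | 1-14% | 15-97% |
| Doubled | 19-87% | 44-100% |

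Type I error of the literal test was about 0-1% throughout.

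**The case against.** The strongest reply is that section 6.3 speaks of differences within the group over time and section 6.1 of a within-participant design. A one-way ANOVA with time as its single factor can then mean a repeated-measures ANOVA. That reading is plausible. Under it the test holds its level and has power similar to a signed-rank test for a rise and modestly lower for a fall. What tells against it is only that the named test is one-way and repeated measures are never mentioned.

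A reader might infer that the trial has almost no power to show benefit or harm on hypoglycaemia. The documents do not support that. They give no rate, spread, correlation or effect size for this outcome. Even the literal test reaches 52% for halving and 87% for doubling in the most favourable settings, and the repeated-measures version does much better. Nor is the shape of the distribution the main cause of the loss.

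It can also be said that safety does not rest on this test. Section 7.3.2 provides fortnightly glucose review, referral of flagged cases, and use of referred cases in the safety assessment; Table 1 prompts adverse event reports. This stands as protection for participants. It does not repair the analysis of a secondary outcome that the protocol sets out to test.

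Finally, summaries for secondary outcomes are often left to an SAP, which is not shown. Here, however, the protocol states a method for every outcome, so the point concerns stated text.

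**Conclusion.** The point holds in limited form. Section 6.3 assigns a summary and a named test that suit a repeated, probably low and skewed count poorly.

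- **Literal reading:** the test is miscalibrated, with type I error of about 0-1%. It may have very low power: 4-9% for a halved rate and 6-15% for an 80% rise at 16 completers, under assumed means of 3-5 per week and CV of 1.0-1.2. Less between-person spread or, in most settings, higher rates raise these figures.
- **Repeated-measures reading:** the power problem largely disappears. What remains is the mean/SD summary and the lack of an interval for the change.

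All power figures rest on assumed rates and dispersion. The change is worth making because the outcome is both an expected benefit and a named risk.

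**What to change.** In section 6.3, state that hypoglycaemia frequency will be summarised by median and IQR, and as a rate per week of sensor wear. State that the within-person change from week 4 to week 16 will be analysed by Wilcoxon signed-rank test, with an estimate of the change and its 95% CI. Say also whether the ANOVA kept for the other outcomes is a repeated-measures one.

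A count model clustered on participant, with wear time as offset and a rate ratio as its result, can be supportive. It should not be the main analysis: a log-rate comparison with robust standard errors rejected 5-10% of the time under no change in the wider grid at 16 participants, so it is mildly anticonservative.

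The cost is a few lines; the analysis can be done in SPSS and needs no new data. The small downside is a less uniform analysis section, with a different summary for this outcome.

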### **6.9 Withdrawal / termination**

Withdrawal from the study will be possible at any time and only data collected about the withdrawing participant up until that point will be included in the study. Participants will be asked for their reason(s) for withdrawing but will be under no obligation to answer. The date of withdrawal and reason for withdrawing (if provided) will be recorded in REDCap. There will be no consequences for withdrawing from the study.

Although unlikely, serious safety concerns may lead the researchers to terminate individual participation in the study or terminate the study entirely. For example, if a participant were to suffer a serious adverse event that was directly attributed to the study intervention. With consideration that the nature of this study is to investigate the effect(s) of a dietary intervention with a high level of professional support, we expect the risk of any adverse events to be minimal.

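### Section 6.3 names One-Way ANOVA for a design that measures the same participants repeatedly; the test should be a within-participant analysis with the week 16 minus week 4 contrast as primary

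*Protocol*

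**What the plan says.** Section 6.1 describes the trial as "A 28-week single arm, within-participant controlled intervention study", and the rationale in section 3 calls for "an interventional study that uses participants as their own controls". Section 9 says "All primary, secondary and additional outcomes will be measured at three time-points": before the control period, at its end, and after the intervention. Table 1 places these at the ends of weeks 0, 4 and 16. HbA1c and a few other outcomes are measured again at week 28.

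Section 6.2 bases the sample size on an HbA1c difference of 0.7 percentage points, a standard deviation of 1.0, 80% power and a 5% significance level. This gives 16 participants, raised to 20 for 20% dropout.

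Section 6.3 is the whole analysis section. It names SPSS, says results will be given as means and standard deviations, and has one inferential sentence: "One-Way Analysis of Variance (ANOVA) will be used to assess the within group differences across time for each outcome". It does not mention repeated measures, a participant effect or a particular comparison of time points.

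**The concern.** One-Way ANOVA, as the term is normally used and as SPSS labels it, compares independent groups. This trial has no independent groups: the levels of the only factor, time, are visits by the same people. The test would put all the stable differences between people into its error term, which is exactly the variation the design sets out to remove. The sample size counts on removing it.

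A real HbA1c change of the size the trial was planned to find could then be reported as not significant. The sentence covers each outcome, so an unfavourable change in insulin dose, hypoglycaemia, lipids or renal markers could be missed in the same way.

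A second problem remains even if the pairing is respected. The objective is low-carbohydrate against habitual diet, and the four-week control period is there to serve that comparison. A test of any difference across time does not make it. Under section 6.5 the control period is not inert: participants test glucose at least six times a day and receive education on carbohydrate counting and food labels. A shift between weeks 0 and 4 is therefore plausible.

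**Working it through.** **Inputs from the protocol.** Difference 0.7, SD 1.0, 80% power, 5% significance level, 16 evaluable, 20 recruited, 20% dropout (all 6.2); three common time points (9). Two-sided testing is assumed, because the protocol does not say. The within-person correlation ρ is not given, so a range is shown.

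**Step 1: reproduce the sample size.**
- Paired, normal approximation: n = ((1.960 + 0.842) × 1.0 / 0.7)² = 16.02, so 16. Then 16 / (1 − 0.20) = 20. Both stated figures are reproduced, with 1.0 read as the SD of the within-person change.
- Independent groups, same inputs: n = 2 × 16.02 = 32.04, so 33 per time point. With 16 per time point, power is about 51%.

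The trial is sized on pairing.

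**Step 2: power and type I error of the two readings.** Simulation with at least 20,000 trials per setting, n = 16, three visits and equal correlation between visits. True means are 0, 0, −0.7 (no change on habitual diet, then the planned effect). The SD of change is held at 1.0, so the per-visit SD is 1 / √(2(1 − ρ)): 1.00, 1.29 and 1.58 at ρ = 0.5, 0.7 and 0.8.

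| ρ | One-Way ANOVA, power | Repeated-measures ANOVA, power | One-Way ANOVA, type I error |
|---|---|---|---|
| 0 | about 81% | about 79% | about 5% |
| 0.3 | 64% | 79% | 1.6% |
| 0.5 | 44% | 79% | 0.5% |
| 0.7 | 16% | 79% | below 0.1% |
| 0.8 | 5% | 79% | below 0.1% |
| 0.9 | 0.2% | 79% | below 0.1% |

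Repeated-measures ANOVA keeps its type I error at about 5% throughout. Both columns are omnibus tests of the same hypothesis, so the comparison is like for like. The cause is the standard error: ignoring the pairing inflates it for a change by 1 / √(1 − ρ), which is 1.4 times at ρ = 0.5 and 2.2 times at ρ = 0.8.

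**Step 3: can the omnibus test isolate the diet?** Put the whole fall before the diet starts: means 0, −0.7, −0.7. The repeated-measures omnibus test rejects about 79% of the time, the same as for a true diet effect of that size. The week 16 minus week 4 contrast rejects 5% of the time, as it should.

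**Step 4: dropout.** With 20% dropout, 4 of 20 participants would lack week 16. One-Way ANOVA would then compare early means from up to 20 people with a late mean from about 16. The resulting shift is the dropout fraction times the baseline difference between dropouts and completers. The protocol gives no figure for that difference, so the size cannot be stated. Classical repeated-measures ANOVA would instead discard the four participants entirely.

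**The case against.** The best defence is that repeated-measures ANOVA was meant. The sentence speaks of within-group differences across time, there is one arm, and time is the only factor, so One-Way may simply mean one-factor. This is plausible, and on that reading the power loss in step 2 disappears. It does not rescue the sentence. The text does not say repeated measures, the named software has a separate independent-groups procedure under the name used, and steps 3 and 4 still apply.

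It can also be said that the primary contrast and the handling of missing visits belong in a statistical analysis plan, and that section 6.3 does not rule out pairwise comparisons after the omnibus test. As omissions alone, these would not be findings. They matter here because the protocol does fix a test, and the sentence needs rewriting anyway.

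A reader might infer that dropping incomplete participants contradicts section 6.9, which says "only data collected about the withdrawing participant up until that point will be included in the study". It does not. That section says which data are kept after withdrawal. It does not define an analysis set, and the retained data could still serve descriptive and safety reporting.

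A reader might also infer that selective dropout will bias the HbA1c result by some definite amount. Any number would depend on an invented baseline difference, so this is a possibility of unknown size.

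Finally, a mixed model is not the only acceptable repair. That is true: stating the repeated-measures form and naming the contrast would settle the main points.

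**Conclusion.** The point stands. As written, the test does not match the within-participant design or the paired sample size, and it governs the primary outcome. Read literally, it lowers power from about 79% to 44%, 16% and 5% at ρ = 0.5, 0.7 and 0.8. The error is conservative: it does not produce excess false positives, and nothing in the documents supports a claim that it would.

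These figures assume 16 completers, equal correlation between visits, an SD of change of 1.0 (the reading that gives n = 16) and a correlation the protocol does not state. If 1.0 were instead the per-visit SD, One-Way power would be about 44%, 41% and 39% at the same correlations, against roughly 79%, 95% and 99% for repeated measures. The conclusion is the same, but that reading is not the one behind n = 16.

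If repeated-measures ANOVA was intended, two weaknesses remain. The omnibus test does not separate diet from control-period drift, and participants with a missing visit are lost from a sample of 20.

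**What to change.** Replace the inferential sentence in section 6.3 with wording to this effect: each outcome will be analysed with a linear mixed model with time as a categorical fixed effect and participant as a random effect, using all observed visits. The primary analysis is the week 16 minus week 4 contrast in HbA1c with its 95% confidence interval. The week 4 minus week 0 contrast is reported beside it as the drift on habitual diet. Where week 28 data exist, that comparison is a separate contrast.

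If ANOVA is preferred, the minimum repair is to state the repeated-measures form, name the week 16 minus week 4 contrast as primary, and say what happens to participants with a missing visit.

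Section 6.2 should also say that 1.0 is the SD of the within-person change, if that is what was meant. An exact two-sided paired t-test of the primary contrast has about 74% power with 16 completers and needs 19 for 80%, so the stated power is slightly optimistic even for the right analysis.

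The cost is a wording change. SPSS fits the model, and no new data or visits are needed. The change should be made before any outcome data are examined.
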